## Methods

### Study Design

This study is designed as a blinded (assessor and statistician), parallel-group, randomized controlled trial. The CONSORT (Consolidated Standards of Reporting Trials) guidelines for clinical trials will be followed [41,42], with reporting on social and psychological interventions [43], and the SPIRIT (Standard Protocol Items: Recommendations for Interventional Trials) guidelines for protocol studies (Multimedia Appendix 1) [44]. The clinical trial was registered on ClinicalTrials.gov (NCT06784245).

### Study Setting and Participants

The Centro Integral del Adulto Mayor (CIAM; Comprehensive Center for Older Adults) in the city of Los Angeles, Biobío region, Chile, will be invited to participate. CIAMs aim to provide care, promotion, and support to individuals aged ≥60 years. These centers are managed by local municipalities and serve as spaces for social interaction and activities, including workshops, meetings, and medical and social care tailored to older adults. CIAM Los Angeles was selected due to its central role as the primary location where older adults from throughout the city gather. This provides access to a diverse group of older adults, including those who are frail and meet the study’s selection criteria. A collaboration agreement was created with CIAM to be able to carry out outcome measurements and the FPT program. In addition, CIAM has a space equipped with a 50-inch smart television and physical activity equipment so that a health professional can guide telerehabilitation sessions.

### Power Calculation

The sample size was calculated a priori using G*Power 3.1.9.7. A total of 52 participants in total are required (26 in each group), considering Cronbach α=.05, 1-β=.8, and effect size=0.8 (lower limb strength based on the results of a previous study) [19]. Considering the possibility of abandonment, 6 participants were added (N=58; n=29 in each group; Figure 1 [42]).

**Figure 1 figure1:**
[figure not shown]
Flowchart of the synchronous telerehabilitation (STR) intervention [41]. FPT: face-to-face physical therapy.

### Recruitment of Participants

All individuals aged ≥60 years belonging to CIAM Los Angeles will be invited to participate. Research support staff will conduct recruitment in person or by telephone. To be eligible for participation, individuals must meet the following inclusion criteria: (1) both sexes aged ≥60 years, (2) older adults from the CIAM, (3) older adults diagnosed with frailty according to the modified Fried phenotype scale [5], (4) ability to stand up and walk ≥10 m without assistive devices, (5) Abbreviated Mini-Mental State Examination >13 points [45], and (6) no medical contraindication for physical exercise. In addition, older adults must have a smartphone or tablet and an internet connection at home. Computer or internet literacy is not required as an eligibility criterion. Exclusion criteria include older adults with fractures, recent acute myocardial infarction, associated cardiovascular pathology, severe acute respiratory failure, high blood pressure, uncontrolled diabetes mellitus, limitations following instructions, as well as individuals participating in another exercise program during the project (Figure 1).

### Randomization

The sample will be selected by quota until a size of 58 participants is reached. The selection will be random among those who meet the inclusion and exclusion criteria. Participants will be randomized by research staff using a computer-generated sequence and concealed allocation to one of the following two groups: (1) the STR group, which will receive STR, or (2) the FPT group, which will receive FPT. A simple randomization computational sequence stratified by gender, age, and frailty will be used to obtain a balance between men and women, age ranges, and severity of frailty in both groups. The randomization sequence will be concealed using sequentially numbered, opaque, sealed envelopes to ensure allocation concealment (Figure 1).

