**Methods:**

In a randomized, blinded, parallel-group controlled trial, all older adults who are frail and aged ≥60 years of both sexes from the Los Angeles Comprehensive Center for Older Adults will be invited to participate. A total of 58 older adults who are frail (aged ≥60 years) meeting the eligibility criteria will be randomly assigned to either an STR group (n=29, 50%) or an FPT group (n=29, 50%). Participants will engage in 1-hour multicomponent exercise sessions twice weekly for 12 weeks. The telerehabilitation group will participate via videoconferencing, supervised remotely by technical staff, while the face-to-face group will attend in-person sessions. Outcomes will include lower limb strength (sit-to-stand test), cardiorespiratory fitness (2-minute step test), upper limb strength (grip strength test), balance (Timed Up and Go, and single-leg stance), quality of life (36-item brief health survey), functional status (functional independence measure), and daily steps (pedometer).

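### Simple randomisation within strata does not secure the balance on gender, age and frailty, or the 29 per arm, that the plan attributes to it

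*Protocol article*

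**What the plan says.** The Randomization section of the protocol article names the method and its purpose in one sentence: "A simple randomization computational sequence stratified by gender, age, and frailty will be used to obtain a balance between men and women". The purpose extends to all three factors: "to obtain a balance between men and women, age ranges, and severity of frailty in both groups". Concealment is by "sequentially numbered, opaque, sealed envelopes". The section also says of enrolment: "The sample will be selected by quota until a size of 58 participants is reached".

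The Power Calculation section gives the planned arm sizes. Before dropout: "A total of 52 participants in total are required (26 in each group". After the allowance: "Considering the possibility of abandonment, 6 participants were added (N=58; n=29 in each group". The Methods paragraph of the abstract repeats 29 per arm, as 50% each.

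No part of the article mentions blocks, minimisation, a biased coin or any other restriction on the sequence. The Statistical Analysis section lists group, time and their interaction as the effects of the repeated-measures ANOVA. None of the three stratification factors is in that model.

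**The concern.** Stratification balances a factor only when assignment within each stratum is restricted, so that the arms are forced to stay close in number. Simple randomisation has no such restriction. The sentence therefore joins a method to a result that the method does not ensure, and the fixed 29:29 has the same problem.

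At stake is the credibility of the baseline comparison in a small trial. The sponsor judged gender, age and frailty severity important enough to balance by design. If the method is carried out as written, balance on them is left to chance, and the stated model offers no adjustment to compensate.

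**Working it through.** **Inputs.** From the article: 58 randomised, 29 per arm planned, 26 per arm required, α = 0.05, power 0.80, effect size 0.8. Not in the article, so assumed below: two-sided testing, the number of men, and the number of strata.

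**1. The plan's sample size reproduces.** Two-sample t test, noncentrality d√(n₁n₂/(n₁+n₂)), two-sided α = 0.05, d = 0.8:
- 25 per arm: power 0.791
- 26 per arm: noncentrality 0.8 × √13 = 2.88, power 0.807

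So 26 per arm is the smallest size that reaches 0.80. A one-sided test would need only 21, so the figure is two-sided. With 10% dropout, 52/0.90 = 57.8, which rounds up to 58. The sample size is not in question.

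**2. Stratifying a simple sequence changes nothing.** In a stratum of size n_s, the number sent to STR is Binomial(n_s, ½), independently of the other strata. Summed over strata it is Binomial(58, ½), however the strata are drawn. Likewise, if m men are enrolled, the number of men sent to STR is Binomial(m, ½). Both are the distributions under unstratified simple randomisation.

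**3. Arm sizes, Binomial(58, ½).**
- Exactly 29:29: C(58,29)/2⁵⁸ = 0.104
- 33:25 or worse: 2·P(X ≥ 33) = 0.358
- 34:24 or worse: 0.237
- 36:22 or worse: 0.087
- SD of the difference in arm sizes: √58 = 7.6

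**4. Balance on a factor, with gender as the example.** The gender mix is not given, so a range is shown. Probability that at least two thirds of the men fall in one arm:

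| Men among 58 (assumed) | Split, at least | Probability |
|---|---|---|
| 12 | 8 in one arm | 0.39 |
| 15 | 10 in one arm | 0.30 |
| 20 | 14 in one arm | 0.12 |
| 29 | 20 in one arm | 0.06 |

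**5. Effect on power (formula of step 1).**

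| Split | Power |
|---|---|
| 29:29 | 0.849 |
| 33:25 | 0.843 |
| 34:24 | 0.839 |
| 36:22 | 0.828 |
| 39:19 | 0.802 |
| 40:18 | 0.791 |

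Power before dropout falls below 0.80 only at 40:18 or worse, which has probability 0.005. Averaged over all splits it is 0.843.

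**6. What a restricted scheme would gain.** Simulation of 8,000 trials, assuming 35% men, other factor levels equally common, and 8 or 12 strata:

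| Scheme | SD of arm difference | P(33:25 or worse) | Mean absolute imbalance among men | P(29:29) |
|---|---|---|---|---|
| Simple | 7.6 | about 0.36 | about 3.6 | 0.10 |
| Blocks of 4, 8 strata | 2.6 | 0.006 | 1.4 | 0.32 |
| Blocks of 4, 12 strata | 3.2 | 0.024 | 1.8 | 0.25 |

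Blocks of 2 raise P(29:29) only to 0.39 (8 strata) or 0.32 (12 strata), because many blocks stay incomplete.

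**The case against.** The strongest reply is that *simple* is loose wording in a condensed article. Recruitment is scheduled to end on May 31 and the intervention to start on June 1, so the sponsor could assemble all 58 and then draw a random half of each stratum, which would balance. Block details are also often kept to a fuller document to protect concealment. This is possible, but the article does not describe such a draw, and sequentially numbered envelopes fit it poorly. Nor is the article silent: it names a method and credits it with a result. If a restricted scheme is intended, the published sentence is still wrong.

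Several further objections do stand and limit the point.

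- **Power.** A reader might infer that the trial is underpowered whenever one arm starts below 26. Step 5 shows otherwise: the larger arm largely compensates.
- **Bias.** A reader might infer that the comparison is biased. It is not. Simple randomisation is valid, and the test's error rate already allows for chance imbalance. The time × group contrast also removes stable baseline differences. What remains is imbalance on factors related to the amount of change, which the model does not adjust for.
- **Envelopes.** A reader might infer a single envelope series that cannot follow stratum-specific lists. The article does not say how many series there are.
- **Stratum-level splits.** The numbers of age ranges and frailty levels are not given, so a figure for lopsided individual strata would rest on invented stratum sizes. Imbalances in separate strata can also offset each other.
- **Exact equality.** Stratified blocks do not guarantee 29:29 either.

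**Conclusion.** The point holds in a limited form. As written, the method does not ensure balance on gender, age and frailty beyond what unstratified simple randomisation gives, and it does not ensure 29 per arm. Exact equality has probability 10.4%, and 33:25 or worse 35.8%. These two figures need only 58 independent 1:1 assignments and no assumption about strata. The figures for men depend on the assumed gender mix, and those for blocks on the assumed strata.

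The harm is avoidable chance imbalance on factors the sponsor singled out, together with a method statement that contradicts its own purpose. The loss of power is negligible and the trial's validity is not threatened. It should be corrected because the correction is cheap, but it is not a fatal flaw. It would be too strong to say that the method cannot produce balance, since it can do so by chance.

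**What to change.** Delete *simple* and name a restricted scheme. Either of these would serve:

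- computer-generated permuted blocks of randomly varying size within a small number of strata, with block sizes withheld from recruiting staff and one concealed envelope series per stratum; or
- minimisation with a random element on all three factors, which copes better with three factors and 58 people.

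Describe the arms as approximately 29 each (1:1). If exactly 29:29 is required, an overall constraint has to be added and stated.

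Before first allocation the cost is a new list, new envelopes and a revised sentence. If strata are kept few by dropping a factor, and that factor is to be adjusted for instead, the analysis model changes as well and must say so. The downside is slightly more predictable allocation, which varying block sizes or the random element, together with concealment, keep small.

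If allocation has already taken place, the list cannot be repaired. The sponsor should then report the method actually used and, if it was simple, withdraw the claim that stratification secured balance.

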### Procedure

Primary outcomes (lower body strength and cardiorespiratory fitness) and secondary outcomes (upper limb strength, dynamic balance, static balance, number of steps, functional status, and quality of life) will be assessed face-to-face 2 weeks before the initiation of the intervention in both groups (Figure 2).

**Figure 2 figure2:**
[figure not shown]
Study design of the synchronous telerehabilitation intervention program.

In addition, at that time, STR group participants will be provided with a tablet and home exercise equipment (exercise mats, resistance bands, cones, and dumbbells). If exercise materials are lost or damaged, they will be replaced. A home visit will be conducted to identify barriers to exercise and assess the most suitable location to carry out the STR sessions. One week before the intervention, there will be 2 induction sessions on the proper use of sports equipment, as well as video calls. Written and verbal instructions will be provided outlining the simple steps necessary to connect to an online meeting and facilitate participation in the STR program, as well as the proper use of the home exercise equipment. In addition to the induction sessions, asynchronous material was provided to address questions related to connectivity and the use of devices such as tablets and watches.

At the beginning of the interventions, all participants will be given a hydration kit (cotton towel and a water bottle) and a smartwatch (Fitbit Inspire 2, Google LLC) to measure continuous heart rate monitoring during exercise sessions to maintain exercise intensity, and pedometer (OMRON HJ-321, Kyoto, Japan) to record the number of daily steps each participant takes. (All the equipment that will be delivered to participants is guaranteed).

During the intervention period, nutrition guidance and exercise education will be provided to all participants once every 4 weeks. Throughout the 12-week intervention period, the participants will be encouraged to maintain the same physical activity levels and calorie intake as before participating in the study. During the education sessions, we will inform the participants to inform the support personnel holding the education sessions about any changes in physical activity levels or nutrition intake. A record will be kept of the number of sessions completed by each participant, which will serve as an indicator of adherence to the program. In addition to session attendance, retention rates (including reasons for nonattendance or withdrawal) and interactions with the technical support team will be recorded.

A postintervention assessment will be conducted after the last week of the 12-week program (Figure 2).

All data collection will be carried out in a face-to-face meeting with older adults at a care center. Technical staff will be trained to ensure an unbiased procedure. Measurements will be taken individually in a place with optimal conditions of privacy, temperature, and humidity. Evaluations will be conducted by health care professionals. The person evaluating will be different from the one performing the interventions.

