### Outcome Measures

#### Overview

Physical fitness, functional status, and quality of life will be examined before and after the interventions. All measurements will be performed by a health professional (technical staff will be trained), blinded to the group allocation scheme, which will guarantee an unbiased procedure. In addition, all measurements will be conducted in a face-to-face setting and obtained individually in an environment with optimal conditions of privacy, temperature, and humidity, such as an older care center collaborating with the project. Data will be recorded on standardized forms and entered into a secure access database that contains quality control checks (eg, range checks and notifications for missing data). The main outcome for this trial will be lower body strength (assessed in the 30-second chair stand test) and cardiorespiratory fitness (evaluated using the 2-minute step test). Secondary outcomes included upper limb strength, dynamic balance, static balance, number of daily steps, functional status, and quality of life.

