##### Number of Daily Steps

Each participant will wear a digital pedometer for 7 consecutive days. The total number of steps recorded during this period will be summed and divided by the number of days the pedometer was worn to calculate the average daily step count. Each participant will receive instructions and an illustrative guide with specific care of the equipment. We will use the classification proposed by Tudor-Locke and Bassett, which indicates that the number of steps represents the level of physical activity: <2500 steps/day (basal activity); 2500 to 4999 steps/day (limited activity); 5000 to 7499 steps/day (low activity); 7500 to 9999 steps/day (mildly active); 10,000 to 12,499 steps/day (active); >12,500 steps/day (highly active) [64].

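### The pedometer is issued only when the interventions start, so the 7-day step count due two weeks earlier cannot be obtained as written

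*Protocol article*

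**What the plan says.** Four places in the protocol article bear on when daily steps are measured.

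- **Procedure, opening paragraph.** The primary and secondary outcomes, with number of steps named among them, "will be assessed face-to-face 2 weeks before the initiation of the intervention in both groups".
- **Number of Daily Steps.** The outcome is an average taken from a wear period: "Each participant will wear a digital pedometer for 7 consecutive days".
- **Procedure, text after Figure 2.** There are two hand-outs. The first belongs to the baseline: "at that time, STR group participants will be provided with a tablet and home exercise equipment". The second comes later: "At the beginning of the interventions, all participants will be given a hydration kit", and the same sentence goes on to list a smartwatch and the "pedometer (OMRON HJ-321, Kyoto, Japan) to record the number of daily steps each participant takes".
- **Statistical Analysis.** The model is a two-way repeated measures ANOVA with group, time (before and after) and their interaction, so each outcome needs a value from before treatment.

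On activity outside the sessions, the Procedure section adds that over the 12 weeks "the participants will be encouraged to maintain the same physical activity levels and calorie intake as before participating in the study". The Objectives section hypothesises that number of steps, among the other outcomes, improves in both arms.

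**The concern.** A 7-day step count cannot be recorded on a device that the participant does not yet have. If the text is followed, either there is no step baseline or it is collected after the programme has started. In the second case the value already contains programme activity. That would tend to raise it in both arms and so reduce any apparent improvement. It may not raise it equally, because FPT participants attend the centre while synchronous telerehabilitation (STR) participants exercise at home. The time × group interaction would then compare changes from a starting point that treatment had already touched. Analysis cannot recover a baseline that was not recorded.

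Two related points in the same section need a sentence each. Participants are encouraged to hold constant their physical activity, which is what the step count is said to represent, without a statement of what that covers. And STR equipment is handed over at the baseline time, without a statement that the baseline tests come first.

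**Working it through.** The plan gives no figure for this outcome to reproduce; its sample size rests on lower limb strength and does not enter here. The check is one of timing. Call the first day of the programme day 0.

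**Inputs**

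| Item | Value | Source |
|---|---|---|
| Step baseline due | day −14 | Procedure, opening paragraph |
| Pedometer issued | day 0 | Procedure, after Figure 2 |
| Wear needed | 7 days | Number of Daily Steps |
| Sessions per week | 2 | STR Program; FPT Program |
| STR induction sessions | about day −7 | Procedure, after Figure 2 |
| Programme ends | 31 August 2025 | Results |
| Last follow-up assessment | by 15 September 2025 | Results |

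**Step 1: can the baseline be met?** The device arrives 0 − (−14) = 14 days after the baseline is due. The earliest complete record ends at 0 + 7 = day 7. That window is programme week 1 and contains 2 scheduled sessions. No 7-day record can exist at day −14.

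**Step 2: what would the week-1 record contain?** For both arms, two exercise sessions, which include walking (Interventions, Overview). For FPT only, attendance at the centre as well. The article does not say whether steps from sessions or travel count, and gives neither distances nor modes of travel.

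**Step 3: can a size be given?** Only under assumption. If attendance adds *s* steps per return trip, the FPT week-1 average rises by 2 × *s* / 7 steps per day:

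- *s* = 0 (for example, driven door to door): 0
- *s* = 1,000: 2,000 / 7 = 286
- *s* = 4,000: 8,000 / 7 = 1,143

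No value of *s* comes from the article. The excess enters the interaction in full only if the post-programme wear week contains no such trips, and the article does not date that week.

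**Step 4: does a proper baseline fit?** With issue at day −14, seven days of wear end at about day −7. That leaves 7 days before the first session and just clears the induction sessions. After the programme, 31 August to 15 September is 15 days, so a 7-day wear fits with 8 to spare.

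**The case against.** The strongest defence is that the schedule is clear and only the hand-out sentence is loose. The Procedure section, the Outcome Measures overview and the Statistical Analysis section all speak of measurement before the intervention. The outcome definition refers to a pedometer without naming the model, so a loaned device could serve for baseline. Figure 2, to which the Procedure section refers, is not shown. What stands of this is limited. The later hand-out is stated, not omitted, and is set apart from the equipment given at baseline. The pedometer's purpose in that sentence is to count daily steps. No loan or pre-programme wear week is mentioned. If Figure 2 gives another schedule, the text still has to be brought into line with it.

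The objection is right about several stronger readings:

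- **That the FPT baseline is inflated by a known amount and will show as a decline.** The steps per trip are pure assumption and the excess may be near zero. Participants already belong to the centre, so some travel there may be habitual in either arm. The post-programme wear week is not dated.
- **That the activity instruction makes a null result on steps uninterpretable, or that steps should cease to be an efficacy outcome.** The wording is encouragement. It applies to both arms and plausibly means activity outside the programme, as a control on co-interventions. It limits how an absence of change can be read. Reclassifying the outcome would be a matter of preference.
- **That participants know their allocation when they perform the effort-dependent baseline tests.** The article puts the STR hand-over at the baseline time but gives no order within it. Testing may come first, and assessors are to be blinded.

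**Conclusion.** The inconsistency holds: the baseline date, the 7-day wear and the hand-out date cannot all be satisfied, and the gap is 14 days. If the text is followed, the pre-intervention step count falls in a week with two sessions, is not pre-treatment, and could differ by arm. This assumes that the issued pedometer is the one used for the baseline, which is the only arrangement described.

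Neither the size nor the direction of a between-arm bias can be established from the article, and it may be small. The timing fault is confined to one secondary outcome and leaves the primary outcomes and the sample size untouched. It is still worth correcting before the first participant starts. The activity instruction and the order of testing and hand-over are matters to clarify, not demonstrated faults.

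**What to change.** 1. Issue the pedometer at the baseline visit two weeks before the start, and amend the hand-out sentence to say so.
2. Complete the 7-day baseline wear before the first session and, where possible, before the induction sessions.
3. Set a matching 7-day wear after the last session, and date it in the text and in Figure 2.
4. State that the encouragement to keep activity constant refers to activity outside the programme, and that it limits how a lack of change in daily steps can be read.
5. State that all baseline tests are completed before allocation is revealed and before STR equipment is handed over.

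The devices are already provided for and the baseline visit already exists. The cost is an earlier hand-out and a few sentences of protocol text. Both wear weeks fit the published calendar.
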